#### The Community Navigators

Community Navigators will be embedded within participating services in Camden and Islington NHS Foundation Trust and Barnet, Enfield and Haringey Mental Health NHS Trust. They have been recruited specifically to this role and do not need a professional mental health qualification. Lived experience of mental health problems constitutes relevant experience, but is not essential. Excellent interpersonal skills, sensitivity to and understanding of mental health difficulties, local knowledge, and awareness of assets in the community are essential requirements for the role. In this feasibility trial, three Community Navigators will be working with participants across Barnet, Camden, and Islington. Recruitment to these posts involved the study working group, who developed exercises to assess applicants’ rapport-building skills and awareness of community assets. Community Navigators will be supported to fulfil their role through training and supervision.

##### Training

A five-day initial training programme provides instruction and practice in key activities of the role: community resource-finding; mapping people’s social worlds; developing a personal social connections plan; using a solution-focused approach [38]; and the GROW coaching model [39]. Training is experiential in nature using group discussion and scenarios. Trainers with lived experience of depression or anxiety will help Navigators to role play tasks offering realistic practice and valid feedback. Practitioners from involved clinical services will also provide training about local service structures and available crisis support, the nature of the participant group, and guidance on how to respond to safety concerns regarding participants or urgent clinical needs. The Community Navigators will also learn through discussion and direct observation of experienced staff employed in social navigation roles at Wellbeing Enterprises CIC and Bromley-By-Bow Centre social prescribing projects.

##### Supervision

Regular group supervision (monthly at each of the two services in this trial) will provide support with delivering the study activities and address issues or challenges in working with specific participants. Supervisors are mental health practitioners from participating services who know the study participants, bring clinical expertise and local service knowledge, and who are familiar with and supportive of the structure and aims of the Community Navigator programme. The Community Navigators will also have immediate access at all times to clinical staff in the event of any immediate concerns about participants’ safety or wellbeing.

### The control group

Participants in the control group (*n* = 10) will be offered written information about community resources and activities within their area. Participants will otherwise receive standard care, unaffected by their participation in the study. This was chosen as a comparator to demonstrate whether support from a Community Navigator is effective over and above usual care received from multidisciplinary teams with enhanced knowledge of resources generally available in the local area.

### Outcome measures

#### Procedure

All participants in the feasibility trial will be asked to complete self-report questionnaires at baseline and at the six-month end of intervention follow-up, through a structured interview with a study researcher. Additionally, 20 participants receiving the intervention, the three Community Navigators and ten other stakeholders (the Community Navigators’ supervisors, and other involved mental health team staff and participants’ involved friends or family) will be asked to take part in a qualitative interview following the intervention. Interviews will explore acceptability of the community navigator programme and views on its impact from several perspectives. This is described in the SPIRIT flow diagram (Fig. 1) and the SPIRIT trial schedule (Table 1).

Information about all study assessments is provided in the participant information sheets, and consent to collect data and contact participants about follow-up is included in consent forms. Written consent from participants will be confirmed before the 6 month follow-up questionnaires are completed. A separate information sheet and written consent from participants will be provided for qualitative interviews. Participants will be offered a £20 gift in cash to thank them for their time at three time-points (upon completion of each of the baseline and follow-up questionnaires and the qualitative interview).

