### Aims

The main aims of the Community Navigator Feasibility RCT are:To develop and manualise a social intervention involving Community Navigator support to increase social connections and reduce loneliness for people with complex depression and anxiety using secondary mental health servicesTo trial the programme with 40 service users to test acceptability of the intervention and trial procedures (including outcome measures and feasibility of participant recruitment and retention) and investigate optimal trial processesTo explore stakeholders’ experience of the programme, barriers and facilitators to its successful implementation, potential mechanisms of its effect, and refine a theory of change model which outlines the processes by which the programme may have an effect

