## Methods

### Design

The study is a feasibility trial with block randomisation conducted in two sites in London (United Kingdom). Randomisation will be stratified by site with an allocation ratio of 3:1, intervention to control. The trial compares Community Navigation, a co-produced, newly developed social intervention provided in addition to standard care from secondary mental health services, to a control group receiving standard care and written information about local community resources.

The design as described here adheres to the Standard Protocol Items: Recommendations for Interventional Trials (SPIRIT) guidelines [26], including a flow diagram (Fig. 1) and a SPIRIT schedule (Table 1). A copy of the SPIRIT Checklist, detailing where each recommended element of the protocol is included in this paper, is provided as Additional file 1.

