### Participants

At each study site, 20 service user participants will be recruited at baseline (total *N* = 40). This sample size has been chosen to be sufficient to give an indication of the acceptability of the Community Navigator programme and the feasibility of trial recruitment procedures. The treatment group will consist of 30 participants and the remaining 10 participants will form the control group.

To ensure that we are working with a population who are experiencing loneliness, we will use the six-item De Jong Gierveld Loneliness Scale [27] as a screening measure, for which a score of 2 has been established as a minimum threshold for loneliness. De Jong Gierveld and colleagues recommend categorising scores of 2 to 4 on this scale as moderately lonely and 5 to 6 as severely lonely [28]. Other inclusion criteria have been kept deliberately broad, although we will prioritise service users currently receiving support from several disciplines (e.g. care coordination, psychology and medical review), to help us explore whether Community Navigation is a useful addition to multi-disciplinary care from a secondary mental health service.

Inclusion criteria:Currently on the caseload of a secondary mental health service for people with depression or anxietyAged 18 years or olderScore at least 2 on the six-item De Jong Gierveld Loneliness Scale [27] at initial screening

Exclusion criteria:People who do not have capacity to consent to participatePeople who pose a risk of harm to others (as judged by their care coordinator) such that meetings with a researcher or Community Navigator are not recommendedPeople who are unable to communicate in English. Resources were not available to deliver this early stage intervention in other languagesPeople who are currently an inpatient at a mental health or general hospital or using mental health crisis services

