#### Qualitative interviews

At or towards the end of their sessions with their Community Navigator (after a minimum of five sessions have been received, or the participant has elected to discontinue meetings with their Community Navigator), a researcher will contact participants for a qualitative interview. Members of the team who will be carrying out the interviews with participants have personal experience of depression and anxiety, and topic guides for all qualitative work will be coproduced with the study working group. These interviews will explore people’s experiences of the programme, including:The content of sessions with Community NavigatorsThe impact of being part of the programmeHow the programme proved helpfulChallenges around being part of the programmeSuggested improvements to the programme

Qualitative interviews will be conducted with participants (*n* = 20), Community Navigators (*n* = 3) and up to ten other stakeholders. These could include the Community Navigators’ supervisors, other clinicians, social care or voluntary sector staff such as peer support workers, and family and friends nominated by participants as important to them in utilising the support. We will purposively sample 20 participants receiving the intervention for a qualitative interview as far as possible to ensure representation from all services and participants with a range of demographic and clinical characteristics, including those who completed the programme of Community Navigation and those who discontinued the intervention early.

These interviews will be used to refine a Theory of Change for this programme. This is a model which outlines the processes by which the programme may have an effect [50]. The Theory of Change will be built around the following components:Assumptions - the context in which the programme is taking place and how it will workInputs - the resources put in to deliver the programmeActivities - the content of the programmeEnablers - factors facilitating the delivery of programme outcomesIntermediate outcomes – the shorter-term changes or impacts of the programmeFinal goals – the broader-longer term aims of the programme

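### Participant interviews cover the intervention arm only although trial procedures are to be tested, and nothing visible puts the six-month questionnaires before the interview

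*Protocol article*

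**What the plan says.** Under Aims, the second main aim is to "test acceptability of the intervention and trial procedures (including outcome measures and feasibility of participant recruitment and retention", and to learn how best to run the trial. The third aim concerns stakeholders' experience of the programme.

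**Who is interviewed.** Outcome measures, Procedure, lists "20 participants receiving the intervention, the three Community Navigators and ten other stakeholders". The Qualitative interviews section under Outcome measures agrees: "We will purposively sample 20 participants receiving the intervention for a qualitative interview". Its five listed topics are session content, impact, helpfulness, challenges and possible improvements, all of the programme. The Qualitative interviews section under Data analysis directs the analysis to the intervention and the Theory of Change.

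**When.** Three places bear on timing:
- Procedure: those selected "will be asked to take part in a qualitative interview following the intervention".
- Qualitative interviews: contact is made at, or close to, the end of a participant's sessions, "after a minimum of five sessions have been received, or the participant has elected to discontinue meetings with their Community Navigator".
- Table 1: the interview is marked in both the treatment-period column and the follow-up column.

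**What the outcomes are used for.** Loneliness and PHQ-9 are self-reported at baseline and six months in both arms. Data analysis, Quantitative measures, plans a between-group mean difference with confidence interval for each. It also says that the trial is too small for clear inference about group differences.

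**The concern.** There are two separate issues.

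First, the second aim covers trial procedures as well as the intervention, but the only method that asks participants for reasons is reserved for people who received a Navigator. Data analysis records recruitment, attrition, adverse events by arm and missing data by randomised group. These show whether controls stayed and completed forms. They do not show how controls found being randomised 3:1, whether the written information was an acceptable comparator, or whether the questionnaires were tolerable to someone offered nothing further. Preliminary testing cannot fill the gap, because all ten people in it had Navigator support.

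Second, the timing statements let some intervention participants reflect with a researcher on what the programme did for them shortly before they rate their loneliness and depression. No control has that contact. Self-report does not protect against priming of the respondent. What is at stake is a clean reading of the two mean differences that are meant to indicate whether the intervention could affect outcomes.

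**Working it through.** **Arm sizes (the plan's own figure).** Inputs: 20 recruits at each of two sites ("At each study site, 20 service user participants will be recruited at baseline") and "Randomisation will be stratified by site with an allocation ratio of 3:1, intervention to control".
- Total: 2 × 20 = 40.
- Intervention: 40 × 3/4 = 30. Control: 40 × 1/4 = 10. Per site, 15 and 5.
- This matches the stated sizes: "The treatment group will consist of 30 participants and the remaining 10 participants will form the control group".

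**Interview coverage.**
- Intervention arm: 20/30 = 67%.
- Control arm: 0/10 = 0%.
- With 5 interviews moved to controls: 15/30 = 50% and 5/10 = 50%, still 20 in total.

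**Can an interview precede the six-month questionnaires?**
1. The Intervention outline lets participants place their meetings anywhere in the six months, up to ten in all. A person's sessions can therefore end, or be stopped by choice, well before month six.
2. The Qualitative interviews section then permits an interview near that point, once five sessions have taken place or the person has chosen to stop. Table 1 agrees, because it marks the treatment period as well as follow-up.
3. The Procedure wording can be read as after the whole six-month period or as after that person's own sessions. On the first reading it conflicts with the other two places. On the second there is no conflict, but an interview can still fall before month six.
4. No visible text says that the questionnaires come first. Fig. 1 is not shown and cannot be checked.

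**How large could the effect be?** The documents give no figure for reactivity to an interview, so s below is an assumption. Let an interview held before the questionnaires shift a person's score by s SD, and let all 20 come first (the worst case). The shift in the mean difference is (20/30) × s − (0/10) × s = 0.67s.

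| Assumed s (SD) | Shift in difference (SD) | Share of CI half-width |
|---|---|---|
| 0.1 | 0.07 | 9% |
| 0.2 | 0.13 | 18% |
| 0.3 | 0.20 | 27% |
| 0.5 | 0.33 | 45% |

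The half-width assumes equal SDs, no dropout and an unadjusted comparison: t(0.975, 38 df) × √(1/30 + 1/10) = 2.024 × 0.365 = 0.74 SD. If every interview follows the questionnaires, the shift is 0.

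**The case against.** The best defence is that the interviews serve the third aim, experience of the programme, and that recipients are the right people to ask. The second aim is covered by the recruitment, attrition, adverse-event and missing-data measures. The questionnaire battery was already shortened after preliminary testing, and the working group advises on trial processes. The topic list is introduced as non-exhaustive and the guides are still to be coproduced. Much of this stands: control-arm feasibility is not unassessed, and control interviews are an improvement rather than the repair of an error. It does not supply the controls' own account, because a wider topic guide cannot reach people who are not interviewed.

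On timing, the five-session rule is a floor within an instruction to interview near the end of sessions. A reader might infer that interviews are freely allowed from the fifth session; the section does not say that. Table 1 and the Qualitative interviews section agree with each other, and only the Procedure phrase is out of line on one reading. That is fair, but the order relative to the questionnaires remains open.

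On bias, intervention participants already have up to ten meetings, up to three group sessions and two feedback calls, so one interview adds little contact, and the protocol disclaims clear inference. This also stands. It limits the weight of the timing point without removing the reason to settle the order.

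A reader might also infer that low attenders are shut out. The same section commits to sampling people who left early, so that is too strong. What remains is a wording gap: someone with fewer than five sessions who drifts away without choosing to stop meets neither stated condition.

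**Conclusion.** The point holds as two modest, inexpensive improvements.

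- **Control arm.** The plan obtains no account from any of the 10 controls of randomisation, the control material or the questionnaires, although acceptability of trial procedures is a main aim. This rests on the text alone.
- **Timing.** The statements need reconciling, and as they stand an impact-focused interview may precede the self-reported outcomes in one arm only. The 67% is the share to be interviewed, and so only a ceiling on the share interviewed early. The bias is at most 0.67s, with s unknown, against a half-width of about 0.74 SD, and is probably small.

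Two stronger conclusions are not supported. A reader might infer that control interviews would explain why people refuse the trial. Consent and baseline data collection precede randomisation, so those who refuse are never controls. A reader might also treat the imprecision of a retention proportion in ten people as evidence on whether the control condition is acceptable. Retention counts bear on who stayed, and acceptability is a different question.

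**What to change.** 1. **Settle the order.** Reconcile Procedure, Qualitative interviews and Table 1 so that each participant's interview follows that person's six-month questionnaires. The cost is scheduling, and longer recall for people who leave early.
2. **Hear from controls.** Within the same total of 20, offer a few interviews (for example about 5) to control participants, and add randomisation, the control material and the outcome battery to the topic guide. The cost is about 15 rather than 20 intervention interviews, with changes to the topic guide, information sheet and consent wording.
3. **Close the wording gap.** State that reaching six months also makes a participant eligible for interview, whatever the number of sessions, so that low attenders who never actively stopped can be sampled as the section intends. This needs one sentence.

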#### Measures

A number of potential primary and secondary outcome measures for a future definitive RCT will be included. These self-report questionnaires will be assessed for response and completeness at baseline and six-month follow-up. The battery of measures for use in the study was reviewed and shortened following feedback from preliminary testing and discussion with the working group. Data collection will begin by asking participants for information on their socio-demographic characteristics including age, gender, ethnicity, marital status, living arrangements, accommodation, and employment. Participants will then be asked to complete the following validated outcome measures, all of which provide data for analysis in continuous form:The De Jong Gierveld Loneliness Scale is an 11-item, self-report measure of loneliness, yielding a total score and subscale scores for social and emotional loneliness [41].The Lubben Social Network Scale is a six-item self-report measure assessing quantity and quality of contact with family and friends [42].The Resource Generator UK is a 27-item measure of perceived access to social capital [43].The Time Budget Diary is a retrospective self-report measure of activity over the previous week [44]. Additional questions have been added to this measure so that participants are asked whether activities were done with others or alone and, if with others, whether this was online, phone or face-to-face. These additions will allow us to distinguish activity involving social contact from other activity.The Warwick-Edinburgh Mental Well-being Scale is a 14-item self-report scale of mental wellbeing [45].The Patient Health Questionnaire (PHQ-9)is a nine-item self-report measure of depression [46].The Generalized Anxiety Disorder Questionnaire is a seven-item self-report measure of anxiety [47].The EQ-5D-5 L is a five-item self-report health outcome measure [48].The Recovering Quality of Life Questionnaire is a 10-item self-report measure of quality of life developed for use across all mental health populations [49].

These measures were chosen by the working group after extensive discussion balancing data collection needs and respondent burden. They aim to capture dimensions which support from a Community Navigator may improve including mental health symptoms (depression, anxiety), social outcomes (loneliness, social network, social capital), day-to-day activity and general wellbeing (mental wellbeing, quality of life).

We will seek information from Trust Informatics teams regarding participants’ current diagnosis, care cluster, attended and missed face-to-face appointments with their mental health team, use of other community mental health services, admission to acute care, days in inpatient care, and use of the Mental Health Act. These records will be sought for the six months prior to baseline and at six months’ follow-up for the intervention period. Participants’ use of social care services will also be sought from local council social care records at the same time points.

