**Methods:**

In this feasibility trial, 40 participants with anxiety or depression will be recruited through two secondary mental health services in London and randomised to an intervention (*n* = 30) or control group (*n* = 10). The control group will receive standard care and written information about local community resources. The coproduced intervention, developed in this study, includes up to ten sessions with a ‘Community Navigator’ over a 6-month period. Community Navigators will work with people individually to increase involvement in social activities, with the aim of reducing feelings of loneliness. Data will be collected at baseline and at 6-month follow-up – the end of the intervention period. The acceptability of the intervention and feasibility of participant recruitment and retention will be assessed. Potential primary and secondary outcomes for a future definitive trial will be completed to assess response and completeness, including measures of loneliness, depression and anxiety. Qualitative interviews with participants, staff and other stakeholders will explore experiences of Community Navigator support, the mechanisms by which it may have its effects and suggestions for improving the programme.

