Support to use this action plan will be person centred and include: providing information about available activities and sources of support locally; practical help to access activity (e.g. planning travel routes or accompanying the participant to a new social group); access to financial support from a budget of £100 per participant; reinforcing strengths and successes; problem-solving challenges and setbacks; and providing encouragement and emotional support to increase social connectedness. Community Navigators can also utilise exercises from the Groups 4 Health programme to encourage people to focus on beneficial social activities and to develop reciprocity and give more to others in social interactions, potentially eliciting more positive responses [35].

Finally, participants will be invited to attend up to three sessions to meet co-participants, discuss the programme’s aims and their progress, and share information about helpful local resources and experiences. One session will be early in participants’ support from their Community Navigator, during the first half of the 6-month intervention period, and one towards the end of the programme. A third session may be added, depending on the enthusiasm for this in the group. Attendance is optional but Community Navigators will encourage and support all participants to join in where possible. Sessions will last approximately 2 h, with a break, and will be facilitated by the Community Navigators. Each meeting will have a loose agenda tailored to the needs of those taking part to achieve maximum impact. The group will follow the principles of the Community Navigator programme with a socially focused, person-centred approach.

The Community Navigation programme is a social intervention focussed on increasing social contact and connection. Community Navigators will be dissuaded from helping participants with other problems (e.g. medication management, housing, employment, debts or welfare benefits), for which they may not have the time or clinical skills, and for which the participant may already be receiving support. Instead, Community Navigators will be encouraged to signpost participants back to the involved clinical team for help with these issues.

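### The questions added to the Time Budget Diary give no stated means of separating programme contact from other social contact in a recall week that ends at the close of treatment

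*Protocol article*

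**What the plan says.** Under Measures, the article describes the diary's window: "The Time Budget Diary is a retrospective self-report measure of activity over the previous week". It then describes added questions by which "participants are asked whether activities were done with others or alone and, if with others, whether this was online, phone or face-to-face", and gives their purpose: "These additions will allow us to distinguish activity involving social contact from other activity". It mentions no category for who the other people were.

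The Abstract fixes the timing: "Data will be collected at baseline and at 6-month follow-up – the end of the intervention period".

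Under Intervention outline, intervention participants may have up to ten one-hour Navigator meetings, placed anywhere in the six months. Practical help can include "accompanying the participant to a new social group". Up to three group sessions of about two hours are offered, one of them early and "one towards the end of the programme". Under The control group, controls receive standard care and written information on local resources.

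Under Quantitative measures, every outcome is summarised overall and by arm, with its missingness. Between-group mean differences with confidence intervals are planned only for loneliness and the PHQ-9. The same paragraph says that the trial is too small for clear conclusions about group differences.

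**The concern.** The diary was adapted to show whether people have more social contact. On a split between alone and with others, an hour with the Navigator looks the same as an hour with a friend. Both are face-to-face activity with another person. Because the recall week runs up to the end of treatment, some of the treatment itself may be inside the window, and controls have no counterpart.

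If such time is counted, the follow-up figure mixes contact that the programme supplied with contact that participants built for themselves. The second is what the intervention is meant to produce, and what a definitive trial would want to measure. One purpose of this trial is to test candidate outcomes for that later trial, so a diary carried forward in this form would take a one-sided shift with it.

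The problem lies mainly in what is recorded. An analysis plan can separate programme contact only if the form, or another record linked to it, identifies that contact.

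**Working it through.** The article states no figure for this quantity, so there is none to reproduce. The check asks how much programme time could fall in a one-week window at the end of a six-month period.

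**Inputs from the article**
- Recall window: 1 week (Measures).
- Period: 6 months, taken as 26 weeks.
- Meetings: up to 10, of 1 h each; timing flexible (Intervention outline).
- Group sessions: 2 planned, a third possible; about 2 h each (Intervention outline).
- Minimum for treatment as per protocol: 3 meetings (Data analysis).
- Control arm: 0 h of programme contact.

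**Assumptions**
- Accompanied outings fall within the meeting hours.
- Baseline social-contact hours are not given, so a range of 5 to 40 h/week is used for scale.

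**Average hours in the recall week, with contact spread evenly (total hours / 26)**
- 3 meetings: 3/26 = 0.12 h
- 10 meetings: 10/26 = 0.38 h
- 2 group sessions: 4/26 = 0.15 h
- 3 group sessions: 6/26 = 0.23 h
- Maximum offer: (10 + 6)/26 = 16/26 = 0.62 h

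**Chance that the recall week holds at least one meeting**

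With m meetings at random times, the chance is 1 − (1 − 1/26)^m:
- m = 3: 11%
- m = 5: 18%
- m = 10: 32%

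With ten meetings in ten separate, evenly spaced weeks, it is 10/26 = 38%.

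**Individual cases**
- One meeting and one group session in the recall week: 1 + 2 = 3 h.
- Last programme contact more than a week before follow-up: 0 h.

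**Scale against the assumed 5 to 40 h/week**
- 0.62 h is 12.4% of 5 h and 1.6% of 40 h.
- 3 h is 60% of 5 h and 7.5% of 40 h.

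Even spreading is a convenience. One group session is deliberately placed late and meeting times are free, so the true average could be above or below these values.

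**The case against.** The strongest reply is that the article gives no scoring rule. A reader might infer that the diary scores Navigator time as social contact, so that the intervention counts itself as an outcome. The text does not say so. It gives the added questions and their purpose, but not how a social-contact total is derived. Coding rules often sit in a full protocol, manual or analysis plan that is not shown. The diary also records activities and is completed in an interview with a researcher, so a Navigator meeting may be recognisable from the entry. Navigators keep a log of each session. This stands against any claim that programme time is in fact counted. It does not remove the point, because the article presents the added questions as what makes the distinction, and as described they do not make it for programme contact.

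Second, little in this trial depends on the diary. It receives no between-group estimate and the article disclaims inference. That is correct, and it limits the consequence to descriptive summaries and the choice of measures for a later trial.

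Third, not all programme contact is artificial. Group sessions let participants meet one another, and an accompanied visit brings contact with the people there. Simple exclusion would discard some genuine contact. This stands, and it favours reporting both ways.

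A reader might also extend the point to the service-use data, because "Community Navigators will be embedded within participating services" and the Trust records cover "attended and missed face-to-face appointments with their mental health team". The article nowhere says that Navigator sessions are entered in Trust systems or counted as team appointments. That extension rests on an unsupported assumption and should not be made.

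**Conclusion.** The point holds in a limited form. As described, the adapted diary has no stated means of telling programme contact from other social contact, and its recall week sits at the end of treatment. Any programme contact in that week, if counted, raises the measure in the intervention arm only.

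Overlap is possible but not certain. A meeting falls in the recall week with a chance of roughly 11% (three meetings) to 38% (ten, evenly spaced). The average shift is at most about 0.6 h/week under even spreading of the full offer, and an individual with a meeting and a group session in that week has about 3 h. How much this matters depends on baseline contact hours, which the article does not give.

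Confidence is high that no means of separation is described, and much lower on the size. The loneliness and PHQ-9 estimates are untouched.

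**What to change.** Add one 'with whom' code to the follow-up diary: Community Navigator, programme group session or study contact. The last covers the feedback calls about sessions and the qualitative interviews with participants, which also occur only in the intervention arm. Report social-contact time with and without the coded entries, and show programme-contact time separately by arm. Reporting both ways avoids having to decide now whether group sessions and accompanied outings are genuine contact.

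The cost is one response code and slightly longer diary administration. Baseline diaries are completed before randomisation and need no change. Recruitment began on 24 April 2017, so the first six-month follow-ups fall around late October 2017. Any follow-up diary completed without the code would have to be coded from its activity entries or from the Navigators' session logs. The article does not say that those logs are dated, so this should be checked before relying on them.
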